#### Gastrointestinal toxicity

Nausea and vomiting should be controlled with standard anti-emetics and will not result in dose modification.

#### Other toxicities

If the patient develops any other grade 3 or 4 toxicity thought to be related to carboplatin, carboplatin should be held until symptoms resolve to ≤ grade 1 or baseline (atezolizumab treatment should continue as scheduled).

### **6.4 Co-medication**

All concomitant medication must be documented in the patients' file. No other anticancer agents or investigational drugs are allowed during the study or within 14 days of the inclusion into the trial, nor the participation into another study.

- ◆ Supportive treatment with anti-emetics is allowed.
- ◆ Palliative radiation to symptomatic lesions is allowed (outside the brain) after start of atezolizumab, as long as the response to atezolizumab can still be evaluated. It is not required to hold atezolizumab during palliative radiotherapy; chemotherapy should be interrupted per institutional standard of care
- ◆ Bisphosphonates are permitted, as long as these have been started at least 1 month ago.
- ◆ Use of G-CSF is not routinely allowed.
- ◆ Subjects are permitted to use topical, ocular, intra-articular, intranasal, and inhalational corticosteroids (with minimal systemic absorption). Physiologic replacement doses of systemic corticosteroids are permitted, even if > 10 mg/day prednisone equivalents. A brief course of corticosteroids for prophylaxis (eg, contrast dye allergy) or for treatment of non-autoimmune conditions (eg, delayed-type hypersensitivity reaction caused by contact allergen) is permitted.

## **6.5 Pregnancy and breastfeeding**

### Pregnancy testing

All women who are being considered for participation in the study, and who are not surgically sterilized or postmenopausal (no menses for more than two years) will be tested for pregnancy within 28 days before enrolment.

### Contraception

Male and female patients will be informed that taking the study medication may involve unknown risks to the foetus if pregnancy were to occur during the study. In order to participate in the study they must adhere to the contraception requirements during the study from the time of screening until 30 days after the last dose of study medication. The following are considered adequate contraceptive methods in this study:

- ◆ Abstinence
- ◆ Placement of a copper intrauterine device (IUD)
- ◆ Male or female sterilisation.

### Breastfeeding

Because of the potential for serious adverse reactions in the nursing infant, patients who are breast-feeding are not eligible for enrolment.

### Pregnancy

If a patient inadvertently becomes pregnant while on treatment, the patient will immediately be removed from the study. The Principal Investigator will immediately be informed. The patient will be followed on a regular basis until the pregnancy has been completed or terminated. The outcome of the pregnancy will be reported as a SAE in case of death, spontaneous miscarriage, congenital anomaly or other disabling or life-threatening complications to the mother or newborn.

If a male patient's partner becomes pregnant on study the pregnancy must be reported to the sponsor. Every effort will be made to obtain permission to follow the outcome of the pregnancy and report the condition of the foetus or newborn to the sponsor.

## 7 Clinical evaluation, laboratory tests, follow-up

### 7.1 Before treatment

#### 7.1.1 Baseline screening

- ◆ Signing Informed Consent
- ◆ Collect fresh biopsies of a metastatic lesion (non-bone) for FFPE and frozen tissue. The biopsy has to contain sufficient tumor content ( $\geq 100$  tumor cells); subjects with samples that have insufficient tumor content will require re-biopsy prior to induction treatment. Collect 3x16 G biopsies (1 for FFPE and 2 for frozen).
- ◆ Confirmation of the lobular histology on a biopsy of a metastatic lesion – or if unavailable on the primary tumor- by local pathologist. Loss of E-cadherin expression or aberrant E-cadherin staining is required.
- ◆ Confirmation of estrogen receptor expression of at least 10% on a biopsy of a metastatic lesion
- ◆ Medical history, including menopausal status
- ◆ Current medication
- ◆ Documentation of persistent toxicities from earlier treatments
- ◆ Full physical examination, including weight and height, blood pressure, pulse and WHO performance status (Appendix B)
- ◆ Laboratory testing: hematology (Hb, leukocytes and differentiation, platelets), biochemistry (glucose, creat, urea, sodium, potassium, magnesium, chloride, calcium, phosphate, albumin, bilirubin,  $\gamma$ GT, AF, AST, ALT, LDH, CRP, TSH, free T4, amylase, lipase, ACTH, cortisol, FSH, LH, E2), serology hepatitis B/C (HbsAg, anti-HBc, HCV Ab), CA15.3, CEA, HIV test, PT and APTT
- ◆ B-HCG pregnancy test in all women of childbearing potential (urine or blood)
- ◆ Electrocardiogram
- ◆ Tumor measurements according to RECIST 1.1 by CT scan thorax/abdomen (not older than 4 weeks at time of start carboplatin)

#### 7.1.2 Before first carboplatin (induction day 1)

- ◆ Symptom directed physical examination
- ◆ Laboratory testing to be repeated if baseline > 3 days ago
- ◆ Blood samples for biobanking (translational research purpose).
- ◆ Collect stool sample for microbiome analysis (optional)

### 7.2 During treatment

#### 7.2.1 Before second cycle of carboplatin (induction day 8)

- ◆ Symptom directed physical exam
- ◆ Adverse events of grade  $\geq 2$
- ◆ Laboratory testing: hematology (Hb, leukocytes and differentiation, platelets), biochemistry (creat, urea, sodium, potassium, calcium, albumin, bilirubin,  $\gamma$ GT, AF, AST, ALT, LDH).

#### 7.2.2 Before start atezolizumab cycle 1/carboplatin no 3 (cycle 1, day 1)

- ◆ Collect fresh biopsies of a metastatic lesion for FFPE and frozen tissue. Biopsies preferably taken from the lesion biopsied at baseline taking into account the risk of complications during the

procedure and sufficient volume of the lesion in case of objective response. Collect 3x16 G biopsies (1 for FFPE and 2 for frozen).

- ◆ Tumor measurements by CT scan thorax/abdomen
- ◆ Symptom directed physical exam
- ◆ Adverse events of grade  $\geq 2$
- ◆ Laboratory testing: hematology (Hb, leukocytes and differentiation, platelets), biochemistry (glucose, creat, urea, sodium, potassium, magnesium, chloride, calcium, phosphate, albumin, bilirubin,  $\gamma$ GT, AF, AST, ALT, LDH, CRP, TSH, free T4, amylase, lipase, ACTH, cortisol, FSH, LH, E2), CA15.3, CEA
- ◆ Blood samples for biobanking (translational research purpose).
- ◆ Collect stool sample for microbiome analysis (optional)

#### 7.2.3 During weekly carboplatin administration (day 8 and 15 of cycle 1,2 and 3)

- ◆ Symptom directed physical exam
- ◆ Adverse events of grade  $\geq 2$  and the Adverse Events of Special Interest for atezolizumab
- ◆ Laboratory testing: hematology (Hb, leukocytes and differentiation, platelets), biochemistry (creat, urea, sodium, potassium, calcium, albumin, bilirubin,  $\gamma$ GT, AF, AST, ALT, LDH).

#### 7.2.4 Before start atezolizumab cycle 2 /carboplatin 6 (day 1 of cycle 2)

- ◆ Symptom directed physical exam
- ◆ Adverse events of grade  $\geq 2$  and the Adverse Events of Special Interest for atezolizumab
- ◆ Laboratory testing: hematology (Hb, leukocytes and differentiation, platelets), biochemistry (glucose, creat, urea, sodium, potassium, magnesium, chloride, calcium, phosphate, albumin, bilirubin,  $\gamma$ GT, AF, AST, ALT, LDH, CRP, TSH, free T4, amylase, lipase, ACTH, cortisol, FSH, LH, E2), CA15.3, CEA

#### 7.2.5 Before start atezolizumab cycle 3/ carboplatin 9 (day 1 of cycle 3)

- ◆ Collect fresh biopsies of a metastatic lesion for FFPE and frozen tissue. Biopsies preferably taken from the lesion biopsied at baseline taking into account the risk of complications during the procedure and sufficient volume of the lesion in case of objective response. Collect 3x16 G biopsies (1 for FFPE and 2 for frozen).
- ◆ Tumor measurements by CT scan thorax/abdomen
- ◆ Symptom directed physical exam
- ◆ Adverse events of grade  $\geq 2$  and the Adverse Events of Special Interest for atezolizumab
- ◆ Laboratory testing: hematology (Hb, leukocytes and differentiation, platelets), biochemistry (glucose, creat, urea, sodium, potassium, magnesium, chloride, calcium, phosphate, albumin, bilirubin,  $\gamma$ GT, AF, AST, ALT, LDH, CRP, TSH, free T4, amylase, lipase, ACTH, cortisol, FSH, LH, E2), CA15.3, CEA
- ◆ Blood samples for biobanking (translational research purpose).
- ◆ Collect stool sample for microbiome analysis (optional)

#### 7.2.6 From atezolizumab cycle 4

##### **During every cycle:**

- ◆ Symptom directed physical exam
- ◆ Adverse events of grade  $\geq 2$  and the Adverse Events of Special Interest for atezolizumab

- ◆ Laboratory testing: hematology (Hb, leukocytes and differentiation, platelets), biochemistry (glucose, creat, urea, sodium, potassium, magnesium, chloride, calcium, phosphate, albumin, bilirubin, γGT, AF, AST, ALT, LDH, CRP, TSH, free T4, amylase, lipase, ACTH, cortisol, FSH, LH, E2), CA15.3, CEA

**Every 6 weeks, every 9 weeks after 6 months:**

- ◆ Tumor measurements by CT scan thorax/abdomen (**official response evaluation**). Measurements should continue until progression, also in case patient is taken off study for another reason.

**Optional (for other centers than the NKI): before start atezolizumab cycle 5 and cycle 7 (day 1 of cycle 5 and 7)**

- ◆ Blood samples for biobanking (translational research purpose).

### **7.3 At progression**

- ◆ For patients who progress after initial response as defined by RECIST: in case a metastatic lesion is accessible and the patient is willing to undergo a biopsy: collect fresh biopsies of a metastatic lesion for FFPE.
- ◆ For patients who progress after initial response as defined by RECIST: collect blood samples for biobanking (translational research purpose)
- ◆ Tumor measurements using CT. Patients may be treated beyond progression under protocol-defined circumstances (see Section 8.1).
- ◆ Laboratory testing: hematology (Hb, leukocytes and differentiation, platelets), biochemistry (glucose, creat, urea, sodium, potassium, magnesium, chloride, calcium, phosphate, albumin, bilirubin, γGT, AF, AST, ALT, LDH, CRP, TSH, free T4, amylase, lipase, ACTH, cortisol, FSH, LH, E2), CA15.3, CEA

### Follow up after progression

- ◆ After progression the patient will go off study. Patient who were referred to the NKI or other study centers for the current study can have their follow up at the referring hospital as long as the NKI or the other study center will be informed regarding date and cause of death. Information on subsequent treatment will be collected.

### **7.4 Ongoing response or stable disease at 12 months (18 cycles)**

Atezolizumab will be given until tumor progression or intolerable toxicity. After 12 months of atezolizumab treatment discontinuation is allowed in case of ongoing response or stable disease. At signs of progression after discontinuation of the treatment, atezolizumab can be re-started. The follow-up in this treatment-free period should be done as follow:

- ◆ Every four weeks: symptom directed physical exam, collect information on adverse events.  
Laboratory testing: hematology (Hb, leukocytes and differentiation, platelets), biochemistry (glucose, creat, urea, sodium, potassium, magnesium, chloride, calcium, phosphate, albumin, bilirubin, γGT, AF, AST, ALT, LDH, CRP, TSH, free T4, CEA, CA15.3.
- ◆ Every eight weeks: CT-scan (after 6 months: every 12 weeks).

## 7.5 Summary table

| Visit description                                         | Screening      | Induc-tion     |                | Cycle 1        |                |                | Cycle 2 |                |                | Cycle 3        |                |                | Cycle 4 | Cycle 5 onwards | At 12 months
(with ongoing response or SD) | At progression | Survival |
|-----------------------------------------------------------|----------------|----------------|----------------|----------------|----------------|----------------|---------|----------------|----------------|----------------|----------------|----------------|---------|-----------------|-----------------------------------------------|----------------|----------|
| Visit window (days)                                       |                | 1              | 8              | 1              | 8              | 15             | 1       | 8              | 15             | 1              | 8              | 15             | 1       | 1               |                                               |                |          |
| Carboplatin                                               |                | 1              | 2              | 3              | 4              | 5              | 6       | 7              | 8              | 9              | 10             | 11             | 12      |                 |                                               |                |          |
| Atezolizumab                                              |                |                |                | 1              |                |                | 2       |                |                | 3              |                |                | 4       | 5->             |                                               |                |          |
| Informed consent                                          | x              |                |                |                |                |                |         |                |                |                |                |                |         |                 |                                               |                |          |
| Confirmation of lobular histology                         | x              |                |                |                |                |                |         |                |                |                |                |                |         |                 |                                               |                |          |
| Biopsy                                        | x  |                |                | x              |                |                |         |                |                | x              |                |                |         |                 |                                               | x  |          |
| Blood for biobank lab                         | x              | x  |                | x  |                |                |         |                |                | x  |                |                |         | x   |                                               | x  |          |
| CT chest/abdomen
(incl tumor measurements)             | x              |                |                | x              |                |                |         |                |                | x              |                |                |         | x   | x                                 | x              |          |
| Medical history, current medication and baseline toxicity | x              |                |                |                |                |                |         |                |                |                |                |                |         |                 |                                               |                |          |
| Physical examination                         | x              | x              | x              | x              | x              | x              | x       | x              | x              | x              | x              | x              | x       | x               | X                                             |                |          |
| Hematology/Chemistry                          | x              | x              | x  | x              | x  | x  | x       | x  | x  | x              | x  | x  | x       | x               | X                                             | x              |          |
| PT/INR and aPTT                                           | x              |                |                |                |                |                |         |                |                |                |                |                |         |                 |                                               |                |          |
| Markers/Endocrinology                        | x              |                |                | x              |                |                | x       |                |                | x              |                |                | x       | x               |                                               | x              |          |
| Pregnancy test                               | x              |                |                |                |                |                |         |                |                |                |                |                |         |                 |                                               |                |          |
| Hepatitis/HIV testing                                     | x              |                |                |                |                |                |         |                |                |                |                |                |         |                 |                                               |                |          |
| ECG                                                       | x              |                |                |                |                |                |         |                |                |                |                |                |         |                 |                                               |                |          |
| Adverse events                               |                |                | x              | x              | x              | x              | x       | x              | x              | x              | x              | x              | x       | x               |                                               |                |          |
| Survival and subsequent treatment                         |                |                |                |                |                |                |         |                |                |                |                |                |         |                 |                                               |                | x        |
| Optional: stool for microbiome analysis                   |                | x  |                | x  |                |                |         |                |                | x  |                |                |         |                 |                                               |                |          |

- 1 3x 16G biopsies: 1 for FFPE, 2 for frozen. Aim at taking sequential biopsies from same lesion
- 2 Mandatory: sufficient number of tumor cells ( $\geq 100$ ) has to be present before patient can enter the study
- 3 Optional
- 4 PBMCs, serum, ctDNA, cfDNA, tumor-educated platelets. At baseline only; material for normal germline DNA. Before cycle 5 and 7 (optional for other centers than the NKI).
- 5 At NKI: material for Breast Immuno Flow (real-time comprehensive analyses off immune cell subpopulations including myeloid cells, [name] lab)
- 6 Every 6 weeks, after 6 months every 9 weeks
- 7 Every 8 weeks, after 6 months every 12 weeks
- 8 Hb, leukocytes incl differentiation, platelets, creat, glucose, urea, sodium, potassium, magnesium, calcium, chloride, bilirubin, gGT, AF, AST, ALT, LDH, CRP, phosphate, albumine
- 9 Hb, leukocytes incl differentiation, platelets, creat, urea, sodium, potassium, calcium, bilirubin, gGT, AF, AST, ALT, LDH
- 10 CA15.3, CEA, TSH, fT4, cortisol, ACTH, amylase, lipase, E2, FSH, LH
- 11 AEs will be graded according to CTCAE 4.03, SAE need to be reported up to 30 days post last atezolizumab study medication infusion
- 12 at baseline full examination, including weight and height, blood pressure, pulse and WHO performance status. During follow-up symptom directed
- 13 only in women of child birth potential

## 8 Response evaluation criteria

Response to treatment will be assessed locally and centrally. Local assessment will be used for treatment decisions during the course of the study and for assessment of the primary endpoint. After completion of the accrual, all scans made for evaluation of the disease of enrolled patients will be reviewed centrally.

### 8.1 Time points of response measurements

RECIST 1.1 measurements during the study will be compared with RECIST at screening. The first official response evaluation will take place after 4 cycles of atezolizumab. In case of initial progression, subjects will be permitted to continue atezolizumab in case of clear clinical benefit as defined in section 8.2 according to iRECIST. [17].

### 8.2 Modified RECIST 1.1 for immune-based therapeutics (iRECIST)

In rare occasions during first evaluation (after 4 cycles) of response to atezolizumab imaging may show small new lesions in the presence of other responsive lesions. In these cases, response evaluation according to iRECIST requires confirmation of progression by a repeat, consecutive assessment no less than 4 weeks from the date first documented, while RECIST 1.1 will define this as PD. If no further progression is seen on the confirmation scan, treatment will be continued according to protocol and imaging will be performed according to the original schedule.

Accumulating evidence indicates a minority of subjects treated with immunotherapy may derive clinical benefit despite initial evidence of PD.[16] At ASCO 2014 it has been presented that conventional criteria such as RECIST [34] may underestimate the benefit of anti-PD1 in approximately 10% of treated melanoma patients. [44] In this view, subjects will be permitted to continue atezolizumab treatment beyond initial RECIST 1.1 defined PD as long as they meet the following criteria (according to iRECIST):

- ◆ Investigator-assessed clinical benefit
- ◆ The possible progression seen on imaging is not putting the patient at risk for tumor-related complications
- ◆ Subject is tolerating study drug

The assessment of clinical benefit should take into account whether the subject is clinically deteriorating and unlikely to receive further benefit from continued treatment. All decisions to continue treatment beyond initial progression must be discussed with the investigator and documented in the study records. Subjects should discontinue study therapy upon further evidence of further progression, defined as an additional 10% or greater increase in tumor burden volume from time of initial progression (including all target lesions and new measurable lesions). New lesions are considered measurable at the time of initial progression if the longest diameter is at least 10 mm (except for pathological lymph nodes, which must have a short axis of at least 15 mm). Any new lesion considered non-measurable at the time of initial progression may become measurable and therefore included in the tumor burden measurement if the longest diameter increases to at least 10 mm (except for pathological lymph nodes, which must have an increase in short axis to at least 15 mm). For statistical analyses that include the investigator-assessed progression date, subjects who continue treatment beyond initial investigator-assessed, RECIST 1.1-defined progression will be considered to have investigator-assessed progressive disease at the time of the initial progression event (according to iRECIST).

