### 3.4 Endpoints

The primary endpoint is:

Proportion of patients who remain free of progression at 6 months. Progression as defined by RECIST 1.1 [34] will be used.

The secondary endpoints are:

- Proportion of patients free of progression (RECIST 1.1[34]) at 6 months in the IR-profile subgroup vs the non-IR-subgroup as defined by gene expression profiling(retrospectively defined as previously described [9])
- Proportion of patients who remain free of progression at 12 months. Progression as defined by RECIST 1.1 [34] will be used.
- Progression as defined by iRECIST [17]
- Overall survival

- Percentage of patients with toxicity (according to CTCAE v4.03, Appendix A) and immune-related toxicity defined as the Adverse Events of Special Interest (AESI's) for atezolizumab (see section 6 and Investigator's Brochure for atezolizumab)
- Objective response rate (RECIST 1.1[34])

*The exploratory endpoints are listed in Section 10 Translational Research*

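### Section 8.2 counts unconfirmed progression as an iRECIST event, against its own confirmation rule, so the investigator-assessed iRECIST endpoint cannot depart from RECIST 1.1 where the two criteria diverge

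*Protocol*

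**What the plan says.** Protocol Section 3.4, like the Synopsis, lists as a secondary endpoint "Progression as defined by iRECIST [17"]. It stands apart from the primary endpoint, "Proportion of patients who remain free of progression at 6 months", which uses RECIST 1.1.

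Section 8.2 explains how the criteria differ. Where the first evaluation shows small new lesions alongside responding ones, "response evaluation according to iRECIST requires confirmation of progression by a repeat, consecutive assessment no less than 4 weeks from the date first documented". The contrast with the conventional criteria is drawn in the same sentence: "while RECIST 1.1 will define this as PD". On a repeat scan that does not confirm, the section adds: "If no further progression is seen on the confirmation scan, treatment will be continued according to protocol".

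Later in Section 8.2 comes the only rule in the protocol for dating progression in patients treated beyond it. Its scope is set by these words: "For statistical analyses that include the investigator-assessed progression date, subjects who continue treatment beyond initial investigator-assessed, RECIST 1.1-defined progression". The consequence for those patients is that each "will be considered to have investigator-assessed progressive disease at the time of the initial progression event (according to iRECIST").

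On the reader, Section 8 says: "Local assessment will be used for treatment decisions during the course of the study and for assessment of the primary endpoint". It also plans central review of all scans after accrual, without naming the criteria or endpoints that this review serves.

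**The concern.** The dating rule is sensible for a RECIST 1.1 endpoint, because treatment beyond progression should not postpone the event. The difficulty is its label and its scope. It is marked as an iRECIST rule, it sits in the iRECIST section, and it applies to every analysis that uses the investigator-assessed progression date. Nothing exempts a patient whose repeat scan shows no further progression, although a few paragraphs earlier confirmation is what separates iRECIST from RECIST 1.1.

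The reason for a separate iRECIST endpoint is to see whether RECIST 1.1 understates benefit with this checkpoint-inhibitor combination. Section 8.2 itself raises that possibility. If a patient with unconfirmed progression followed by stable disease or response is a failure under both criteria, the endpoint cannot inform that question. Agreement between the two analyses could then be read as evidence that pseudoprogression did not occur, when the dating rule produced it.

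**Working it through.** **Step 1: the plan's own figures.** The inputs are in Section 9.2: 22 patients in stage 1, stop at 2 or fewer; 40 in total, reject the null at 8 or more; rates 10% and 25%.

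P(reject | p) = sum over x = 3 to 22 of C(22, x) p^x (1 − p)^(22 − x) × P(Bin(18, p) ≥ 8 − x)

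- p = 0.10: 0.0398, against a stated type I error of 0.04.
- p = 0.25: 0.8032, against a stated power of 80%.

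Both reproduce. They rest on the RECIST 1.1 primary endpoint, so nothing below changes them.

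**Step 2: go through the types of patient.** Compare the investigator-assessed RECIST 1.1 date with what Section 8.2 gives for iRECIST.

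| Patient | RECIST 1.1 | iRECIST by the dating rule | iRECIST by the confirmation requirement |
|---|---|---|---|
| (a) No RECIST 1.1 progression | No event | No event | No event |
| (b) Progression, treatment stopped | Event at first progression | Not covered by the rule | Not stated |
| (c) Progression, treated on, later confirmed | Event at first progression | Event at first progression | Event; date not stated separately |
| (d) Progression, treated on, not confirmed | Event at first progression | Event at first progression | No event from that scan |

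Row (d) is the contradiction: two statements in Section 8.2 give opposite answers for the same patient. It is also the only group for which the protocol describes the two criteria as diverging. In row (c) the rule gives a reasonable date, and the fix below keeps it.

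**Step 3: how many patients row (d) might hold.** The protocol gives no figure for lobular breast cancer or for this regimen. The nearest is in Section 8.2: RECIST may understate benefit in about 10% of melanoma patients treated with anti-PD1. Take an assumed share q of 40 patients, with expected number 40q and P(at least one) = 1 − (1 − q)^40.

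| Assumed q | Expected of 40 | P(at least one) |
|---|---|---|
| 3% | 1.2 | 1 − 0.97^40 = 0.70 |
| 5% | 2.0 | 1 − 0.95^40 = 0.87 |
| 10% | 4.0 | 1 − 0.90^40 = 0.985 |

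Under the dating rule the number in row (d) classified differently by the two criteria is 0 whatever q is. If unconfirmed progression were not an event, it could be up to 4 at q = 10%, which is 4/40 = 10 percentage points. For a proportion at a fixed landmark that is an upper bound, since such a patient must also stay free of confirmed progression up to the landmark.

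**The case against.** The strongest reply is that the iRECIST label is a drafting slip. The sentence speaks of RECIST 1.1-defined progression and dates that event. Sections 8.1 and 8.2 elsewhere use the same phrase for the criteria for continuing treatment, so it may simply be misplaced here. The endpoint in Section 3.4, with its cited reference, and the confirmation requirement would then govern the iRECIST analysis. This is a plausible reading, and it means the text cannot be taken as a deliberate choice to equate the two endpoints. But the label is then wrong and must still go, and the two statements must still be reconciled. Nor can the matter simply be left to an analysis plan: a plan applying the confirmation requirement would conflict with the protocol as written.

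Several stronger inferences are tempting and not supported:

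- *Every patient has the same status and date under both criteria.* The protocol does not state the iRECIST status of patients who stop at first progression (row b).
- *Pseudoprogression can never show.* The rule covers investigator-assessed dates only. Central review might show such cases, although the protocol does not say that it uses iRECIST or feeds this endpoint. The spider plots in Section 9.5 could show later shrinkage.
- *About 10% of these patients are affected.* The figure concerns melanoma and understated benefit in general. Section 8.2 calls its own scenario rare.
- *Four patients matter against the 8 needed for success.* Success is judged on RECIST 1.1, so the comparison has no bearing.

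**Conclusion.** The point holds as a contradiction within Section 8.2, confined to the investigator-assessed iRECIST secondary endpoint. Read literally, the dating rule counts unconfirmed progression as an iRECIST event and removes the one difference from RECIST 1.1 that the protocol describes.

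The size is modest and uncertain: about 1 to 4 of 40 patients, on assumed shares of 3% to 10% that the documents do not establish for this disease. The conclusion itself rests on the wording and not on those shares. It deserves correction because otherwise agreement between the two criteria in this group would be built in and could be misread as a finding. It gives no reason to doubt the primary analysis or the stage 1 decision.

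**What to change.** In Section 8.2, limit the dating sentence to RECIST 1.1 analyses (the primary endpoint and the other RECIST 1.1 progression endpoints) and delete the parenthetical iRECIST label. Add one sentence for the iRECIST endpoint: progression that is not confirmed as Section 8.2 requires is not an event, and confirmed progression is dated at its first documentation.

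Three details can be left to the SAP: how patients without a confirming scan are handled, whether the local or central reading is used, and the summary measure.

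The cost is two sentences and a second derivation of the progression date. Section 8.2 already provides for the confirmation scan and for imaging to continue afterwards, so no further scans are needed. The change concerns analysis definitions only; it alters no treatment rule and leaves the primary endpoint as it is.
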